### Study design and population

The study design will be a community-based cluster randomized controlled trial with both control and interventional arms. Four hundred pregnant women at second trimester of pregnancy (gestational age from 13 weeks and above) living in peri-urban areas of Dodoma City at the time of data collection and willing to participate will be included in the study. Pregnant women with special medical conditions, such as epilepsy, sickle cell anaemia, diabetes mellitus, hypo- or hyperthyroidism, malignancy disease, hypertension, human immunodeficiency virus, ante-partum haemorrhage, renal disease and severe anaemia will be excluded from the study. ANC card and health worker will assist in identifying the eligible participants.

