### Intervention

Previous studies have shown that the use of nutritional education intervention, FEFO supplementation in combination with appropriate IPTp of malaria and de-worming during pregnancy reduces the prevalence of anaemia [25]. This community-based nutritional intervention will consist of the following four components: nutritional education, FEFO supplementation, de-worming and provision of IPTp.

Nutritional education

Nutrition education will be delivered by a research team member using a developed education material. The education material (see Supplementary file 1) has been developed by a research team after doing an intensive literature review from previous studies [26, 27]. The developed educational material has been modified and translated to Swahili language in order to suit our environment. Each pregnant woman in the interventional group will receive nutritional education. Nutrition education consists of the followings: definition of anaemia, symptoms of anaemia, causes for anaemia, effects of anaemia, behavioural and dietary risks for developing anaemia and prevention of anaemia. Nutritional education will be delivered during all three phases of the study. The first phase will be delivered at the time of baseline study where hard copy of education material will be provided to each participant for self-learning. The second phase will be followed 1 month after the first, and the last phase will be carried out 1 month after the second phase. Hard copy of training material will be provided only during the first phase (baseline survey), but the same education material will be used to train pregnant women about nutritional education for all the three phases of the study. The nutritional education training will be provided in groups of 10–11 women. Sessions will be interactive and are expected to last for ∼45–60 min.

ii. Supplementation of FEFO tablets

All participants in the interventional and control arms will receive one tablet of FEFO (200 mg of dried Ferrous Sulphate + 0.25 mg Folic Acid) supplement once daily as per ANC national guidelines [28] during the entire course of the study period. The FEFO supplements will be given on monthly dose basis starting at the baseline survey. Nurse midwifery will dispense the monthly dose of FEFO supplements to each participant. Monitoring of adherence to FEFO supplementation will be carried out on a monthly basis during follow-up visits.

iii. Malaria prophylaxis

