### Sample size calculation and selection

The sample size will be calculated based on the formula for a randomized control study [29].
$$n=\frac{{\left\{Z\alpha \sqrt{\left[\pi o\left(1-\pi o\right)\right]}+Z\beta \sqrt{\left[\pi 1\left(1-\pi 1\right)\right]}\right\}}^{2}}{{\left(\pi 1-\pi o\right)}^{2}}$$
where *n* is the minimum sample size, *Zα* is the standard normal deviate (1.96) at 95% confidence level for this study, *Zβ* is the standard normal deviate (0.84) with a power of demonstrating a statistically significant difference before and after the experiment between the two groups at 90%. *πo* is the proportion at pre-intervention (baseline prevalence of anaemia 50%). *π*1 is the proportion after intervention (prevalence of anaemia after intervention proportion 35%).
$$178=\frac{{\left\{1.96\sqrt{\left[0.5\left(1-0.5\right)\right]}+0.84\sqrt{\left[0.35\left(1-0.35\right)\right]}\right\}}^{2}}{{\left(0.35-0.5\right)}^{2}}$$

With the adjustment for 10% attrition, the calculated sample size will be *n* = 198 (178/0.9). Therefore, a total of 200 pregnant women from each arm (interventional and control) will be recruited for the study. The study arms will be matched in the ratio of 1:1. A list of all wards will be obtained from the administrative authority of Dodoma City. From the list, wards from peri-urban areas will be listed and assigned random numbers. Simple random sampling technique will be used to select four peri-urban wards. Two wards based on geographical area will be assigned to the interventional arm and the remaining two wards to the control arm. From each ward, community health workers and local leaders will recruit eligible participants and invite them at a recommended and agreed place to conduct the study.

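### The sample size rests on a before-after fall in anaemia (50% to 35%), but the trial compares two arms that share three of the four intervention components

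*Protocol article*

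**What the plan says.** The article's section on sample size calculation and selection defines its two planning proportions by time, not by arm. The first, πo = 50%, "is the proportion at pre-intervention (baseline prevalence of anaemia 50". The second, π1 = 35%, "is the proportion after intervention (prevalence of anaemia after intervention proportion 35". The sentence on power then runs the two ideas together, aiming at a "statistically significant difference before and after the experiment between the two groups at 90" per cent. The section gives no expected end-line prevalence for the control arm.

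The Intervention section names four components of the intervention: nutritional education, FEFO, de-worming and malaria prophylaxis with SP. Three of them go to everyone. For FEFO the text reads "All participants in the interventional and control arms will receive one tablet of FEFO", and the paragraphs on SP and mebendazole open in the same way. The Abstract confines education to the interventional arm.

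The comparison of interest is between arms. Outcome measures sets the change in haemoglobin in the interventional arm against that in the control arm, and Data processing and analysis compares the arms by independent t-test. The first objective in the Introduction is a reduction in the prevalence of anaemia.

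**The concern.** A between-arm sample size needs the outcome expected in each arm at the same time point. Here the first proportion describes women before anything is given, and the second describes women after the intervention, which by the protocol's own definition is all four components. The difference of 15 points is therefore a before-after change under the full package. The between-arm effect is a different quantity: what education adds to FEFO, SP and mebendazole.

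The two agree only if prevalence in the control arm stays at 50% while its women take the shared components. The article neither states nor argues this. If control prevalence moves, the contrast to be detected may not be 15 points, and the stated power does not describe it. This calculation is the only justification given for 200 women per arm. If the true contrast were smaller, a null result could be taken as showing that education does not work when the trial had little chance of showing an effect of that size.

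**Working it through.** **Inputs from the sample size section.** πo = 0.50; π1 = 0.35; Zα = 1.96 (two-sided 5%, implied); Zβ = 0.84; attrition 10%; 200 recruited per arm.

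**The plan's own figure.** Putting the printed inputs into the printed formula:

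(1.96 × √0.25 + 0.84 × √0.2275)² / 0.15² = (0.9800 + 0.4007)² / 0.0225 = 1.9062 / 0.0225 = 84.7, or 85 and not the printed 178.

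The attrition step is right: 178 / 0.9 = 197.8, or 198, rounded up to 200. The failure to reproduce 178, and the use of 0.84 (the value for 80% power) beside a stated 90%, are separate faults. Correcting them would leave the question of which contrast is being sized untouched.

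**Which contrast the figures describe.**

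| Component | Interventional arm | Control arm |
|---|---|---|
| Nutritional education | yes | no |
| FEFO | yes | yes |
| SP | yes | yes |
| Mebendazole | yes | yes |

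- Planning contrast: before any component (50%) versus after the intervention (35%).
- Tested contrast: all four components versus three of them, during follow-up.

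**How much it could matter.** No control end-line prevalence is given, so the control values below are assumptions. Completers per arm: 200 × 0.9 = 180. Clustering by ward is ignored, which is optimistic. For a two-sided 5% comparison of two proportions, with d the difference and p̄ the mean of the two:

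power = Φ{ [d√n − 1.96 √(2p̄(1 − p̄))] / √[p_c(1 − p_c) + p_i(1 − p_i)] }

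Worked case, 50% versus 35%: d√n = 0.15 × √180 = 2.0125; p̄ = 0.425, so √(2 × 0.425 × 0.575) = 0.6991; √(0.2500 + 0.2275) = 0.6910. Then (2.0125 − 1.96 × 0.6991) / 0.6910 = 0.929, and Φ(0.929) = 0.82.

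| Scenario | Control | Intervention | Difference | Power |
|---|---|---|---|---|
| As planned, read as two arms | 50% | 35% | 15 points | 82% |
| Control falls, intervention stays at 35% | 45% | 35% | 10 points | 49% |
| Control falls further, intervention stays at 35% | 40% | 35% | 5 points | 16% |
| Both lower, education still adds 15 points | 45% | 30% | 15 points | 84% |
| Both lower still, education still adds 15 points | 40% | 25% | 15 points | 86% |

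The second and third rows follow from reading 35% as the result of the whole package. The last two follow from reading 15 points as the effect of education alone. The text as written supports the first reading, but it does not exclude that the authors meant the second.

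**The case against.** The strongest defence is that 50% already stands for women under routine care. The Discussion describes FEFO, SP and mebendazole as standard care under national guidelines, and the Introduction says prevalence remains high although these measures are in place. The 50% is also below the one Dodoma figure cited, 63.8%. The section names a randomised design, refers to two groups and sizes each arm, so baseline prevalence may have been meant as a loosely worded stand-in for control.

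Part of this stands: 50% is not shown to be wrong. But the article does not make the argument, and its rationale points partly the other way. The Introduction attributes persisting anaemia to women who miss antenatal care or book late, and so take up the tablets and prophylaxis less well. The trial gives control women monthly FEFO with adherence checks, observed monthly SP and observed mebendazole. A routine-care baseline is not automatically an end-line value under that delivery.

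A reader might go further and infer that the shared drugs are known to lower control prevalence, citing the Intervention section's statement that "FEFO supplementation in combination with appropriate IPTp of malaria and de-worming during pregnancy reduces the prevalence of anaemia". The sentence as a whole begins with nutritional education and concerns the combination; it says nothing about the drugs without education. A reader might also infer that the exclusions, which include severe anaemia, push baseline prevalence below 50%. The article does not say which population the 50% describes, nor what fraction is severely anaemic, so that cannot be established.

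It is also fair to object that power need not fall at all, as the last two rows of the table show, and that the primary outcome is haemoglobin change, to which none of these powers applies.

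**Conclusion.** Wrong as written, and it should be fixed. The planning proportions are defined as before and after, while the trial tests arm against arm with education as the only difference. Taken literally, the calculation assigns the before-after fall of a four-component package to one component, and 50% is unsupported as the control arm's end-line prevalence.

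The size is conditional. With 180 completers per arm, a two-sided 5% test and no allowance for clustering, power runs from about 82% down to 49% and 16% if control is 50%, 45% or 40% and the intervention arm is 35%. It stays at about 84% to 86% if education still adds 15 points to a lower control value. The documents do not say which case applies.

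A reader might conclude that the trial could not have detected the effect of education. That is not shown: the size and direction of any control-arm change are unknown, and the powers are for an end-line prevalence test, not for the primary t-test on haemoglobin change. Nor does the wording of the two proportions establish that a within-arm change will be offered as evidence of effect.

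**What to change.** In the sample size section:

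- Define πo as the prevalence of anaemia expected at end-line in control women receiving FEFO, SP and mebendazole, and π1 as that expected at end-line when education is added. Give the basis for each.
- Delete the words about before and after the experiment from the power sentence, so that it refers only to the difference between arms.
- Restate the power of the fixed 200 per arm over a stated range of control end-line prevalences, for example 40% to 50%, and say for each whether the intervention value or the education effect is held constant.
- Say that this power is for end-line prevalence and not for the primary haemoglobin comparison.

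The cost is rewording one paragraph and, probably, a less favourable power statement. Enrolment, allocation, outcomes and treatment are unchanged.

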### Randomization

The unit of randomization will consist of wards. Wards from peri-urban areas will be grouped into two groups based on geographical area (Eastern and Western wards). A total of four wards will be randomly selected as follows: two wards from the East and remaining two wards from the West part of the city. The two groups of wards will be randomly assigned to the study arms as follows: one group to the interventional arm and another group to the control arm, respectively. This will be carried out to ensure that interventional wards are bundled together but far away from control wards in order to minimize contamination. A statistician who will not be the part of this study will do the final randomization of wards to the interventional and control arms.

The flow chart of the study design is shown in Fig. 1.

**Figure 1: bpab012-F1:**
[figure not shown]
Study design and flow chart.

### Data collection

Baseline survey

A cross-sectional survey will be conducted in four selected peri-urban wards. Data will be collected by using a developed semi-structured questionnaire. The questionnaire has been adapted from the Food and Agricultural Organization [27] and modified to suit this study objective (see Supplementary file 2). The questionnaire consists of the six parts, namely, part 1—Demographic information; part 2—Obstetrics history; part 3—Utilization of ANC services; part 4—Knowledge about anaemia (definition, symptoms, causes, prevention, effects, behavioural and dietary risks and preventive measures); part 5—Current dietary practices; and part 6—Maternal health characteristics (anthropometric, haemoglobin and blood pressure).

Data collection will be conducted by researchers and research assistants through face-to-face interviews using the developed questionnaire. Researchers and research assistants will consist of the following professionals: nutritionists, public health specialists and registered nurses–midwife. Nutritionists and public health specialists will administer the questionnaire and provide nutrition education. Registered nurse will be responsible for pregnancy confirmation, measurements of gestational age and administering of FEFO, SP and mebendazole. Haemoglobin measurements will be conducted by the experienced laboratory scientist/technician. Haemoglobin concentration will be measured from a single drop of capillary blood via a finger prick. Prior to interview, researchers/research assistants will explain the purpose of the study to the study participants, and written or verbal informed consent will be taken from participants. Pregnant women found to have severe anaemia will be given a referral letter to a nearby health facility for further investigation and management.

ii. Intervention and follow-up surveys

Participants in the interventional and control arms will be followed up monthly for two consecutive visits. During follow-up, participants in both arms will be checked for haemoglobin concentration and continue to receive FEFO supplements, and SP as per ANC national guidelines [26]. In addition, participants in the interventional arm will receive nutritional education.

iii. End-line survey

An end-line survey will be conducted in both arms. The questionnaire filled out at baseline information will be used to collect data during end-line survey. Haemoglobin measurements will also be carried out. FEFO and SP will continue to be provided as per ANC national guideline [28].

### Measurement of variables

Dependent variable

Dependent variable in this study will be haemoglobin concentration. The haemoglobin concentration will be classified as follows: normal haemoglobin ≥11 g/dl and anaemia <11 g/dl [4].

ii. Independent variables

The independent variables include: demographic characteristics, obstetrics characteristics, utilization of ANC services, knowledge about anaemia (definition, symptoms, causes, prevention, effects, behavioural and dietary risks and preventive measures), current dietary practices and maternal health characteristics (anthropometrics and blood pressure). Other independent variables include still birth, APGAR score, birth weight and new-born mortality.

### Data processing and analysis

Data will be cleaned, edited and coded before data analysis. Statistical Package for Social Sciences version 25.0 will be used to analyse the data. Descriptive statistics will be used to generate frequency distribution, mean, standard deviation and cross tabulation to describe the characteristics of the study participants. The comparisons between interventional and control arms will be determined using independent *t*-tests and comparisons within groups (pre/post) will be estimated using paired *t*-tests. The *P* <0.05 will be considered statistically significant. Regression analysis will be conducted to determine the predictors of haemoglobin concentration.

### Dissemination of results

The findings of this study will be presented at the University of Dodoma. Further, the findings will be communicated to the local community where this study will be conducted. Furthermore, the findings will be presented with the Ministry of Health, Community Development, Gender, Elderly and Children. In addition, we will aim to publish the findings in a suitable peer-reviewed academic journal and present these at local and international conferences.

### Ethical clearance and consent to participate

This study was submitted to the Directorate of Research, Publications and Consultancy of the University of Dodoma for ethical approval. The ethical committee has assessed and given the ethical approval for this study. Furthermore, the permission to conduct this study will be sought from the office of Dodoma Regional Administrative Secretary, District Medical Officer and ward, respectively.

The participants will have the absolute right and freedom to withdraw from the study at any time with no effect to them. Confidentiality and anonymity will be maintained by the use of code numbers on the questionnaire rather than names. Pregnant women who will be found severely anaemic will be assisted by the research assistants to seek proper treatment at the healthcare facility.

## Discussion

This will be the first cluster randomized control trial designed to evaluate the effectiveness of nutritional education intervention on anaemia among pregnant women in Tanzania. This will complement existing antenatal interventions that aim at combating anaemia among pregnant women, one of the greatest nutritional health burdens among women in Tanzania [8–10]. The cluster randomized control trial design, whereby groups of individuals are randomly allocated to different interventions, has the potential to provide unbiased estimates of the impact of interventions delivered at the community level.

Dodoma region produces various food crops, including maize, sorghum, millet, sunflower and nuts. Livestock, such as cattle, goat and chickens, is also raised and marketed within the region. However, previous studies conducted in Dodoma have reported limited awareness of the benefits of food diversity intake and thus dietary intake is often characterized by solely a single food group [30], high consumption of dark green vegetable and low consumption of meat and meat products among women [31]. This study has therefore been designed to assess the benefits of intervention that aims to provide intensive nutritional education on dietary intakes and practices, which enhance iron bioavailability, knowledge on symptoms, causes, effects and preventive measures of anaemia among pregnant women. Parallel with nutritional education, FEFO supplementation, SP and mebendazole will be provided to all study arms (interventional and control) to ensure that all individuals have received standard routine of care as per ANC national guidelines [28].

In Tanzania, utilization of maternal health care services is low [22] and such that only 24% of women attend their first ANC visits in the first trimester, while the majority (73.5%) of women attend in the second and third trimesters of pregnancy [7]. Reasons for low utilization and late attending for ANC services include living far away in remote village areas (hence fear of being harmed when going to the health care facility) and lack of money for transport [32]. This intervention is designed to be conducted in a community-based setting to enable easy and timely access of services by all pregnant women. Community healthcare workers and leaders will be involved for the mobilization of pregnant women towards the selected centres within the community.

The need for effective intervention studies addressing anaemia is particularly relevant to rural communities, where the prevalence of anaemia is highest and the majority of people are poor and less educated. This study will focus on peri-urban areas of Dodoma City. Dodoma is one of the regions with high prevalence of anaemia during pregnancy [10]. It has been reported that anaemia was associated with maternal death in 38.6% of cases in Dodoma region from 2007 to 2011 [33].

In most developing countries, micronutrients deficiencies and parasitic infections particularly malaria and hookworm have been reported to be strongly associated with anaemia during pregnancy [9, 11–13]. Furthermore, inadequate intake of diets rich in iron is reported to cause 75% of iron deficiency anaemia during pregnancy [11, 12, 15, 16]. A major strength of this trial is that it attempts to assess the contribution of nutritional education towards reducing anaemia and also to maximize early utilization of maternal health services among the pregnant women. Proper nutrition education will improve dietary intakes while using community health worker and local leaders, many more pregnant women will be identified and initiated into ANC services. It is hoped that this approach will be effective in reducing anaemia in pregnancy, thereby reducing perinatal morbidity and mortality.

The intensive nutrition education and the teaching material that will be provided to each pregnant woman in interventional and control arm at baseline and end-line survey, respectively, are expected to bring into positive changes to dietary habits in the future. If successful, such an approach could profoundly brings into the attention of the relevant authorities on how anaemia could be controlled using both, diet-focused and supplementation-focused approaches. If effectiveness in real-life conditions is determined, all the above features of the intervention could be scaled-up nationwide, and taken into consideration to improve the outcome for other conditions in pregnancy. In order to maximize policy relevance, it is essential to understand the context of the research, the related policy making processes and to engage key stakeholders. To achieve this, we intend to engage continuously with the health authorities from local to national levels.
